**Fig. 4 fig0004:**
[figure not shown]
Photo of the ASPB field technician with an entomological aspirator. Photo by [name].

### Adult mosquito collection

Our ASPB field technician uses an entomological aspirator (Improved Prokopack Aspirator Model 1419 from John W. Hock Co., powered by a 12 v 9.0 Ah valve-regulated, rechargeable sealed lead battery) to collect adult mosquitoes at specified drains. Wearing gloves, the technician assembles the aspirator consisting of the vacuum and the sample collection vesicle on-site. Holding the aspirator at a minimum one-meter horizontal distance from the drain, the technician approaches the drain and prepares for mosquito capture. The technician stomps on the drain to disturb resting mosquitoes and prompts them to take flight while simultaneously using the aspirator to capture escaping mosquitoes or those resting nearby. The technician subsequently opens the storm drain and systematically vacuums the interior space and walls to capture any resting mosquitoes. If water is present in the drain, the technician vacuums the walls closest to the water at arm's length, as mosquitoes tend to rest in these areas. If there is no water, the technician vacuums at arm's length to cover the entire interior space.

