### Interventions

Our intervention, i.e., mosquito-proofing modification of storm drains, is implemented by our partners at the Barcelona water infrastructure authority, BCASA. We first place honeycomb bricks at the base of the drain to provide structural integrity and subsequently added concrete to create a gradient. We connect the lowest point of the gradient to the discharge pipe, enabling the water to flow down the gradient to prevent water accumulation (Fig. 3). This rapid and low-cost mosquito-proofing intervention is intended to eliminate stagnant water in the catchment drain, rendering the drain unsuitable for mosquito reproduction.

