### Outcomes

Our objective in this trial is to assess the impact of storm drain modifications on *Ae. albopictus* and *Cx. pipiens* mosquito numbers inside intervention and control drains. Our primary outcome is the combined total counts of adult *Ae. albopictus* and Cx. *pipiens* mosquitoes sampled at each drain. The secondary outcome is drain activity defined as the presence of either adult mosquitoes or *Ae. albopictus* and *Cx. pipiens* larvae (L1-L2, L3-L4, and pupae stages) in drain water inside the drains. We sample water elements to collect adult mosquitoes and larvae at these alternative breeding sites. We also measured the depth of water (cm) in corresponding drains. One trained ASPB technician measures the primary and secondary outcomes starting on 26 June 2023 and continuing until no mosquitos are detected, visiting each participating drain once per week.

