#### Implementation

We wrote an *R* script for the selection of drains. The intervention allocation arm (i.e., intervention or control arm) was randomly assigned the letter code A or B, and two sets of shapefiles for the locations of selected drains were generated. The first showed both the intervention arm and letter code assignment for ASPB and BCASA, which are responsible for implementing the storm drain modification and collecting entomological data; the second included only the letter code which we shared with the blinded biostatisticians conducting the analysis. ASPB and BCASA used the allocation results and inspected the drains assigned to the intervention arm for the feasibility of the modification. If the modification was not possible, we assigned the next eligible drain.

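### As written, the aspiration rule behind the primary count depends on whether the drain holds water, which is what the intervention is meant to change

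*Protocol article*

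**What the plan says.** - **Outcome.** Outcomes section: "Our primary outcome is the combined total counts of adult" *Ae. albopictus* and *Cx. pipiens* at each drain. The adults are collected by aspirator.
- **Steps given before any wet/dry distinction.** Adult mosquito collection has the technician stamp on the drain and aspirate escaping insects. Then: "The technician subsequently opens the storm drain and systematically vacuums the interior space and walls to capture any resting mosquitoes".
- **Wet drain.** "If water is present in the drain, the technician vacuums the walls closest to the water", at arm's length, because mosquitoes tend to rest there.
- **Dry drain.** "If there is no water, the technician vacuums at arm's length to cover the entire interior space".
- **What the intervention does.** Interventions section: the modification is "intended to eliminate stagnant water in the catchment drain". The 22 control drains are left unmodified and are described as breeding sites. Under Eligibility criteria, part of the sample was chosen because standing water had been seen in January to March 2023.
- **What is recorded.** Presence and depth of water at each visit (Data collection).
- **Analysis.** Statistical methods names a Negative Binomial mixed model with a random effect for drain. Sensitivity work covers weather, land cover, within-drain correlation and outcome distribution. Nothing is named for the mode of sampling.

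**The concern.** Whether a drain holds water is a consequence of treatment, arising after randomisation. If it also decides where the aspirator goes, the measurement of the primary outcome depends on treatment. Randomisation cannot balance that. A random drain intercept cannot remove it either, because the capture difference runs along the arm contrast itself.

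The estimated rate ratio would then be the true ratio multiplied by a ratio of average capture fractions. If the wet rule misses adults resting elsewhere in the drain, control counts are too low and a real reduction is understated. If searching near the water is the more efficient search, the reduction is overstated. The trial is meant to inform a city-wide decision, so an error in either direction matters.

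**Working it through.** **The plan's own figure.** Power calculation states at least 90% power for a 35% difference with 44 drains at 5%. This cannot be reproduced from the article, because the control mean and dispersion are left to the S1 File. The point does not depend on it; the figure only supplies the design effect, a ratio of 0.65 if the difference is a reduction.

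**Inputs (all assumed; the article gives none of them).**
- pC, pI: shares of control and intervention visits with water. Base case 0.8 and 0.1.
- f: catch under the wet rule divided by catch under a whole-interior sweep of the same drain.

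**Formula.** Observed ratio = true ratio × (pI·f + 1 − pI) / (pC·f + 1 − pC).

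In the base case the distortion factor is (0.1f + 0.9) / (0.8f + 0.2):

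| f | Factor | True 0.65 seen as | True 1 seen as | abs(ln factor) |
|---|---|---|---|---|
| 0.9 | 0.99/0.92 = 1.076 | 0.70 | 1.08 | 0.07 |
| 0.8 | 0.98/0.84 = 1.167 | 0.76 | 1.17 | 0.15 |
| 0.7 | 0.97/0.76 = 1.276 | 0.83 | 1.28 | 0.24 |
| 4/3 | 1.033/1.267 = 0.816 | 0.53 | 0.82 | 0.20 |

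**Other degrees of separation, true ratio 0.65.**
- Complete (pC = 1, pI = 0; factor 1/f): 0.72, 0.81 and 0.93 for f = 0.9, 0.8 and 0.7; 0.49 for f = 4/3.
- Weaker (pC = 0.6, pI = 0.2): 0.68, 0.71 and 0.75; 0.58 for f = 4/3.

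**Against the design effect.** abs(ln 0.65) = 0.43, so every base-case shift in the table is smaller than the effect the trial is powered for. To cancel it fully the factor must be 1/0.65 = 1.538. Solving 0.1f + 0.9 = 1.538(0.8f + 0.2) gives f of about 0.52: the wet rule would have to lose nearly half the catch.

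**Illustration of lost power.** Assume 22 drains per arm, one measurement each, control mean 20, dispersion k = 0.15 and a two-sided 5% Wald test on the log ratio. The variance is (1/20 + 1/(20 × ratio))/22 + 2 × 0.15/22. At 0.65, power is 87%. At the 0.76 seen with f = 0.8, holding the observed control mean at 20, it is 52%.

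**A limit of the formula.** It treats abundance as equal at wet and dry visits within an arm. Strictly, pC and pI are the shares of mosquitoes present at wet visits. If adults in both arms were found only at wet visits, both shares would be 1 and the factor would be 1.

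**The case against.** The strongest objection is the sentence that comes before the split. It has the technician vacuum interior space and walls, with no condition on water. The two water sentences may then only say where to concentrate within a sweep common to all drains, and the catch area would not differ. This reading is possible, but the section does not say so: only the dry rule asks for aspiration at arm's "length to cover the entire interior space". The ambiguity stands, and the authors can resolve it in one line.

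The wet rule also targets known resting places, and the stamping step is common to all drains. Both could bring f close to 1. No figure in the article shows that they do. A smaller swept area would by itself bias towards no effect, which is conservative for claiming benefit; the opposite bias needs the further assumption that the wet search is more efficient.

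A reader might infer more than the article supports:
- **That the arms are always sampled differently.** The rule follows water at the visit, not arm. Control drains can be dry and modified drains can hold water, and no wet-visit frequencies are given.
- **That the missing sweep time is a defect.** Data collection refers to a separate sampling protocol, not shown, which may fix it.
- **That effort is also uneven because the technician knows the arm.** The agencies "which are responsible for implementing the storm drain modification and collecting entomological data" do hold the allocation file, but nothing shows uneven effort. An arm-free working list would not help, since the modification can be seen once the drain is opened.

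**Conclusion.** The point holds on the text. Read literally, the rule for collecting the primary count depends on a consequence of treatment, and neither the stated model nor the sensitivity analyses deal with it. It falls away only if every drain already receives the same full sweep.

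The documents fix neither the direction nor the size. Under the assumed 80% and 10% wet visits, a true 0.65 would be seen as roughly 0.70 to 0.83 when the wet rule catches 90% to 70% of a full sweep, and as about 0.53 when it catches one third more. A reader might conclude that the distortion is as large as the 35% effect itself. That needs f near 0.52 in the base case, and nothing in the article supports so low a value. The bias is material under moderate assumptions and negligible if f is close to 1.

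**What to change.** 1. **State one rule.** Every drain, whatever its water status, gets a full-interior sweep of the same area and duration. If this is already the practice, say so and reword the two water sentences. The cost is a short change to the sampling text and perhaps a minute per visit.

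2. **For visits already made under a split rule**, add a sensitivity analysis that rescales wet-visit counts by an assumed capture ratio, using the recorded presence of water. In the log-link model this is a known constant, ln f, at wet visits and zero at dry ones. Report the treatment ratio over a stated range of f on both sides of 1, and the f at which the conclusion changes. This needs no record of sweep effort, which the article does not say is kept.

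3. **Do not add water presence as a covariate for this purpose.** Water lies on the causal path, so adjusting for it would remove part of the effect being estimated.

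4. **Downside.** If the rule changes mid-season, capture may shift mainly in wet drains, which are mostly controls. That would create a difference between arms that varies over time and could reach the September estimate. Record the change date and also estimate the effect separately before and after it.

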### Larval sampling

Our technician collects a water sample from the drain to assess the presence of mosquito larvae. After submerging the dipping tool (volume 0.5 L with a 1.5-meter long handle) vertically into the water, our technician withdraws the dipping tool to pour the water sample into a designated container [17]. Using pipettes, our technician individually extracts larvae and transfers them into vials. When the water level is low and predominantly contains organic matter such as dirt and debris, we use a hand collector to gather the larvae. We send the vials to the laboratory for species determination. If possible, our technician approximates the number of larvae in the drain stratified by larvae development stages (i) L1-L2 stages, and (ii) L3-L4 stages, and (iii) pupae.

### Laboratory evaluation and storage of biological specimens

Following collection, we transfer the samples to the ASPB laboratory, where they will be stored at −20 °C. We morphologically identify samples using a stereoscope to classify them by species (in the case of *Culex*, to species complex) and sex. We store mosquito samples (by assigning a unique identifying number) for at least two years following the completion of the trial.

### Buffer zones

We investigate the effects of modifying main trial storm drains on adult mosquito counts in alternative mosquito breeding sites. These include water infrastructure features within a 10-meter radius around the main trial drains.

## Statistical methods

Our main analyses are complemented by sensitivity analyses to establish the causal effects of mosquito-proofing storm drains on primary and secondary outcomes. The main analyses focus on the time-averaged and highest effects of the intervention on primary and secondary outcomes. For the combined total adult *Ae. albopictus* and *Cx. pipiens* mosquito counts, i.e., our primary outcome, we assume a Negative Binomial distribution and within-subject independence based on our analyses for the sample size and power calculation. We quantify the effects of the intervention vs. control drains on the primary outcome using a generalised linear mixed model (GLMM), applying random effects for storm drains. We aim to report one effect estimate that is time-averaged and one for September 2023 to demonstrate the highest estimated effect of the intervention. We selected September based on the 2022 data showing the peak of mosquito numbers in Barcelona (see S1 File, the sample size and power calculation section). We further investigate intervention effects by stratifying total adult mosquito counts by species (*Ae. albopictus* and *Cx. pipiens*), sex and month. We report statistically significant effect estimates when the *p*-value is below 0.05.

In our sensitivity analyses, we assess the distribution of land cover characteristics between the control and intervention drains. We also evaluate the assumptions underlying regression analyses, using historical data. Further, we account for variations in weather elements such as relative humidity and temperature, which are assumed to be spatially similar across both arms but could vary based on the timing of measurements. These adjustments aim to reduce uncertainty in the intervention effect estimate. If land cover characteristics are unevenly distributed between the arms, we refine the models to account for land cover effects. To explore our assumptions, we first re-evaluate within-subject correlation, fitting the generalised estimating equations model (GEE) to our data. Second, we explore the primary outcome distribution, fitting intercept-only generalised linear models with Poisson and zero-inflated Poisson distributions. In case of deviation from the assumed distribution and/or independence, we conduct further sensitivity analyses using appropriate modelling approaches.

Prior to conducting regression analyses, we clean the data, tabulate descriptive statistics, and perform data visualisation [30].

All data analyses will be performed using *R* [28]. Scripts for data analyses will be checked and validated by the two analysts and posted in an open GitHub repository using R-markdown [31] following publication of trial results.

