### Trial design

IDEAS trial is a causal evaluation of a structural modification of urban storm drains envisioned by the Barcelona city administration to address mosquito-related threats and nuisances. We leverage the planned implementation to conduct a robust experimental study. Together with the governmental stakeholders, we designed a trial outlined in this protocol. We conduct a parallel-arm randomised controlled trial where eligible storm drains are randomised 1:1 to receive the mosquito-proofing intervention (intervention arm) or not (control arm). We selected eligible drains based on the detection of mosquito activity in 2022/2023 by the Barcelona Public Health Agency. We created a 200-meter zone around each eligible drain to account for mosquito dispersal capacity [[22], [23], [24], [25]] and minimise the risk of contamination across trial arms. We will measure outcomes in the intervention and control storm drains and in water bodies in the vicinity of the drains to capture mosquitoes that may be flying to experimental drains from nearby breeding sites. The overall design is illustrated in Fig. 1.

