### Power calculation

We based our power calculation on the primary outcome to detect at least a 35% difference in mosquito count between the intervention and control arm at a significance level (p-value) of 5%. We explored within-class correlation and the statistical distribution of our primary outcome using data on adult mosquitoes collected in 2022 by ASPB using data from artificial intelligence (AI)-driven smart traps [27]. Our analysis showed independence between weekly measurements, and the data followed a Negative Binomial distribution. Therefore, we performed the power calculation in *R* [28] using the *power_NegativeBinomial* function of the PASSED package ([28,29]). Assuming a minimum detectable difference in mosquito counts of 35% between the intervention and control arms and a significance level of 5%, we estimate a statistical power of at least 90% value for our sample of 44 drains. Further details of the power calculation are given in S1 File (Section: power calculation).

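### The time-averaged and September estimates are both main analyses at 0.05 with no ranking, and September is called the 'highest' effect only because counts peaked then in 2022

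*Protocol article*

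**What the plan says.** All of this is in the protocol article, under Statistical methods. The section opens with "The main analyses focus on the time-averaged and highest effects of the intervention on primary and secondary outcomes". It then names the two estimates: "We aim to report one effect estimate that is time-averaged and one for September 2023 to demonstrate the highest estimated effect of the intervention". The reason given for the month is "We selected September based on the 2022 data showing the peak of mosquito numbers in Barcelona", with a reference to the sample size section of the S1 File. There is one decision threshold: "We report statistically significant effect estimates when the *p*-value is below 0.05".

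Neither this section nor the Abstract, which also lists the two effects together, puts one estimate above the other. The primary outcome itself is clear: under Outcomes it is the combined count of adults of the two species at each drain. The same Statistical methods section also plans effects by species, sex and month.

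**The concern.** There are two separate faults.

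**No ranking.** There is one primary outcome, but two main estimates of the intervention effect on it, both read against 0.05. If they disagree, the text does not say which one answers the trial's question. A reader who accepts either as evidence of effectiveness is working at an error rate above 5%. This matters because the Abstract says the results will guide a city-wide expansion. The Limitations section also expects the steering committee to recommend ending the trial once significant effects are seen, without saying for which estimate.

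**The label.** The month was chosen on abundance, and the label describes effect size. These are different quantities. On a relative scale, the month with the most mosquitoes has no particular claim to the largest effect. The planned results by month could therefore contradict a headline that calls September the highest.

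**Working it through.** **Inputs from the article**
- Two main estimates of the primary outcome and a threshold of 0.05 (Statistical methods).
- Weekly visits from 26 June 2023 until no mosquitoes are detected, so the number of weeks is not fixed (Study setting, Outcomes).
- Independence between weekly measurements (Power calculation).
- A 35% difference between arms as the target (Power calculation).

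**Assumptions**
- Two-sided tests (sidedness is not stated).
- September supplies 4 weekly visits out of a season of 14 to 26.
- Weeks are equally informative.
- Log link and rate ratio (neither is stated).

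The article gives no overall error rate to reproduce. Its power figure (at least 90% for 44 drains) cannot be recomputed, because the mean and dispersion are not in the article. The point does not depend on it.

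**1. Correlation between the two estimates.** The September visits are a subset of the season's visits. With independent, equally informative weeks, the correlation is √(4/M) for a season of M weeks:
- M = 26: √(4/26) = 0.39
- M = 20: √(4/20) = 0.45
- M = 14: √(4/14) = 0.53

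If weeks within a drain are in fact correlated, or if September dominates the information, the correlation is higher. I therefore also take 0.7, 0.8 and 0.9.

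**2. Chance of at least one false positive.** Under no effect, this is 1 − P(|Z₁| ≤ 1.96 and |Z₂| ≤ 1.96), with (Z₁, Z₂) bivariate normal with correlation ρ:

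| ρ | Chance of at least one false positive |
|---|---|
| 0.39 | 9.3% |
| 0.45 | 9.2% |
| 0.53 | 9.0% |
| 0.7 | 8.3% |
| 0.8 | 7.8% |
| 0.9 | 7.0% |

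**3. Does a peak in counts imply the largest effect?** Read the 35% target as a constant ratio of 0.65, and take illustrative control means (not from the article):

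| Month | Control mean | Intervention mean | Ratio | Difference |
|---|---|---|---|---|
| July | 4 | 2.6 | 0.65 | 1.4 |
| August | 6 | 3.9 | 0.65 | 2.1 |
| September | 10 | 6.5 | 0.65 | 3.5 |
| October | 5 | 3.25 | 0.65 | 1.75 |

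The season ratio is (2.6 + 3.9 + 6.5 + 3.25) / (4 + 6 + 10 + 5) = 16.25 / 25 = 0.65, the same as in September. The absolute difference is largest in September and the ratio is not.

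In an illustrative simulation with a constant ratio (five months, control means 4, 6, 10, 5 and 2, dispersion parameter 1, 22 drains per arm, 4 visits a month), September showed the largest estimated relative effect in about 19% of draws. Chance alone among five equal months would give 20%.

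**4. What each remedy costs in power.**
- Ranking the time-averaged estimate first leaves its test at 0.05, so its power is unchanged.
- Splitting the level to 0.025 each would cost power. A test with exactly 90% power at 0.05 has an expected Z of 1.960 + 1.282 = 3.242. At 0.025 the critical value is 2.241, so power is Φ(3.242 − 2.241) = 84.1%.

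**The case against.** The strongest reply has three parts.

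- **No success rule is stated.** The article promises to report two estimates and does not say that either one alone would count as success. A full protocol or analysis plan, not shown here, may rank them. This stands as a caution: the error rate above describes what the text permits, not a declared decision rule. It does not remove the point, because the article itself gives both estimates main status and one threshold.
- **September is fixed in advance.** This is correct, and it is a real safeguard. A reader might infer that the month is picked after seeing the results and so is exaggerated by selection. The article does not support that. Pre-specification settles the choice of month, but not the ranking or the word 'highest'.
- **The scale is unstated.** On the absolute scale with a constant ratio, the peak month does have the largest effect, as the table shows. So the label is defensible on that scale. It is not on the relative scale that the model and the 35% target suggest.

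Other stronger readings also fail:
- The 9.75% for two independent tests cannot apply, because the estimates share data.
- Counting four tests across both outcomes overstates the problem, because the outcomes are already ranked as primary and secondary.
- The threshold sentence might be read as a plan to withhold non-significant results. In full, it most naturally defines significance.
- That the power statement does not name its estimate is no fault of the article, since it refers the details to the S1 File.

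**Conclusion.** The concern holds in a limited form. As written, two unranked main estimates of one primary outcome, each read at 0.05, carry a chance of at least one false positive of about 7.0% to 9.3%. That range assumes two-sided tests and a correlation between 0.9 and 0.39, and it applies if either estimate may be taken as the answer.

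The label 'highest' has no support beyond a peak in 2022 counts. On an assumed relative scale September need not show the largest effect, and under a constant ratio it equals the time average. It may still turn out largest; the plan gives no reason to say so beforehand. Both faults lie in wording that the article itself fixes, and both should be corrected.

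**What to change.** In Statistical methods:

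1. Name the time-averaged effect on total adult count as the sole primary estimate, tested at two-sided 5%, and state its scale.
2. Rank the September estimate below it, tested only if the primary estimate is significant.
3. Rename September 'effect in the expected peak-abundance month', and show it beside the estimates for all other months with 95% confidence intervals.
4. Label the analyses by species, sex and month as exploratory.

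This returns the error rate on the primary question to 5% with no loss of power for the time-averaged estimate. The change is to wording only. The downside is that a significant September result without a significant season-long result could no longer be claimed as success.

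### The GEE check of independence targets marginal correlation, while the primary Negative Binomial GLMM needs independence only given the drain; a check of serial dependence within drains would fit better

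*Protocol article*

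**What the plan says.** All of this is in the Protocol article.

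- Power calculation, on the 2022 smart-trap data: "Our analysis showed independence between weekly measurements, and the data followed a Negative Binomial distribution".
- Statistical methods carries this into the primary analysis: "we assume a Negative Binomial distribution and within-subject independence based on our analyses for the sample size and power calculation".
- The next sentence there names the model: "using a generalised linear mixed model (GLMM), applying random effects for storm drains".
- The same section gives the check on trial data: "we first re-evaluate within-subject correlation, fitting the generalised estimating equations model (GEE) to our data". It then gives the consequence: "In case of deviation from the assumed distribution and/or independence, we conduct further sensitivity analyses using appropriate modelling approaches".
- Outcomes makes the data longitudinal by "visiting each participating drain once per week".

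The article does not say whether independence is meant marginally or given the drain. It also leaves open which working correlation the GEE uses and what result would count as a deviation. Two headline effects are planned, one time-averaged and one for September 2023, plus results by month.

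**The concern.** A drain random effect lets drains differ in level, and so implies that two weeks from the same drain are correlated. What the model assumes is that no dependence remains once the drain level is accounted for. A GEE working correlation measures the total correlation between weeks, drain level included. The planned check therefore looks at a quantity that the primary model does not assume to be zero.

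Stable drain differences are likely here. Under Eligibility criteria, the sample mixes drains with mosquito activity in 2022 and drains added only because standing water was seen in early 2023.

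Two errors are possible. The team may report a violation that is only drain heterogeneity, and then move to further models that are not named. Or, if it looks at one pooled correlation, it may overlook short-range week-to-week dependence, which makes standard errors too small for effects estimated over a few adjacent weeks.

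**Working it through.** **The plan's own figure.** The only related figure is power of at least 90% with 44 drains. The article sends the mean, the dispersion and further detail to S1 File and does not fix the number of weeks, so this figure can be neither reproduced nor refuted. It does depend on independence. With a Wald test on the log rate ratio, variance (1/mu0 + 1/mu1 + 2/k)/n, ratio 0.65, two-sided 5%, mu0 = 3 and k = 1, power is 22% with one measurement per drain and 97% with 10 independent weeks. The GEE is a sensible check of that marginal assumption.

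**Inputs for the rest.** From the article: 44 drains, 1:1, weekly visits, a 35% difference. Assumed: 16 or 20 weeks, mean 3, NB size k = 1, and the variances and AR coefficients below.

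**Step 1: GLMM exactly right.** With marginal mean mu and drain SD s on the log scale, the correlation between any two weeks is

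mu²(exp(s²) − 1) / [mu + mu²(exp(s²)(1 + 1/k) − 1)].

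- s = 0.8: 9 × 0.896 / (3 + 9 × 2.793) = 8.07 / 28.14 = 0.287.
- s = 0.5: 9 × 0.284 / (3 + 9 × 1.568) = 2.56 / 17.11 = 0.149.

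Simulated exchangeable GEEs (200 trials of 20 weeks per scenario) averaged 0.26 (5–95% range 0.17 to 0.37) and 0.14 (0.08 to 0.21). A separate simulation (150 trials of 16 weeks, drain variance 0.5 and 1.0) gave 0.22 and 0.31, above 0.05 in every run.

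**Step 2: GLMM wrong, purely serial dependence.** At lag l the numerator becomes mu²(exp(s² × rho^l) − 1). With rho = 0.6 and s² = 0.5, the denominator is 3 + 9 × 2.297 = 23.68. Lags 1, 2 and 3 then give 0.133, 0.075 and 0.043. The average over all pairs of 16 weeks is 0.036. Simulated exchangeable GEEs averaged 0.03 (variance 0.5) and 0.04 (variance 1.0), above 0.05 in only 13% and 33% of runs. Stronger dependence does register: 0.16 with half of the log-variance serial at AR 0.8, and 0.12 with all of it serial at AR 0.9.

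**Step 3: correlations by lag.** Simulated means at lags 1, 2, 4 and 8:

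- correct GLMM, variance 0.5: 0.22, 0.21, 0.22, 0.21;
- AR 0.6, variance 0.5: 0.12, 0.07, 0.02, 0.00;
- drain effect plus AR 0.6, total variance 1.0: 0.24, 0.19, 0.14, 0.13.

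Flat against decaying separates the cases on average. Single trials overlap: lag 1 exceeds lag 8 by more than 0.10 in 11 to 13% of correct models and in 54 to 84% of serial ones.

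**Step 4: effect on the September standard error.** Take a four-week mean and the Step 2 case. The true variance factor is 1 + (6 × 0.133 + 4 × 0.075 + 2 × 0.043)/4 = 1.296. A model that sees only the average correlation uses 1 + 3 × 0.036 = 1.108. The ratio of standard errors is √(1.108/1.296) = 0.92, so about 8% too small. Other assumed inputs and another linear approximation (11 to 16% at AR 0.6) give an overall range of about 5 to 16%. The false-positive rate is 2Φ(−1.96 × (1 − shortfall)): 6.3% at 5%, 8.1% at 11% and 10.0% at 16%.

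Model fits under no effect agree in size. A pooled arm-by-month GLMM gave 6.6% when right, 6.8 to 7.0% with half the variance serial (AR 0.8) and 8.3 to 8.4% with all of it serial (AR 0.9). A separate four-week fit gave 5.9%, 5.0% and 6.7%.

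**Step 5: time-averaged effect.** Over all weeks, the average correlation is exactly what sets the variance of a drain's mean, so in this approximation the standard error ratio is 1.

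**The case against.** The strongest reply is that the article states no working correlation, threshold or decision rule, and that such details belong in the full plan. The assumption is also traced to the power analysis, where independence is marginal, and a GEE is a fair tool for that. Both points stand. What remains is that the section names a GEE as its check on the trial data without separating the marginal assumption of the power calculation from the conditional one of the GLMM.

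A reader might infer more, and the document does not support it:

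- **That a GEE cannot reveal serial dependence.** It can, if correlations are read by lag (Step 3). The article does not exclude this.
- **That real dependence would go unnoticed.** The stronger serial scenarios also give clearly positive correlations and would prompt further models. Only weaker, short-range dependence under an exchangeable summary is at risk.
- **That this is the plan's sole protection.** The section also evaluates regression assumptions on historical data. A GEE with the usual robust standard errors (not stated in the article) would itself tolerate serial dependence. The 2022 data used to support independence came from smart traps, though, not from aspiration inside drains.
- **That the main result is at risk.** A false alarm costs an extra sensitivity model, and the time-averaged estimate is unaffected.

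The separate four-week fits also show little or no inflation, because an intercept fitted within one month absorbs much of the dependence.

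**Conclusion.** The point holds in limited form. The planned check addresses marginal correlation, and the primary model needs conditional independence. Under the assumed inputs, a correct GLMM yields a GEE correlation of about 0.14 to 0.26, and purely serial dependence at AR 0.6 yields about 0.03 when summarised by one number. That ordering is the wrong way round for a diagnostic of this model.

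The inferential cost is modest, about 5 to 16% on September and monthly standard errors. At the low end, and where September is fitted separately, it is negligible. Every figure rests on assumed weeks, means, dispersion, variances and AR coefficients, none of which the article gives. This is a low-severity, cheap improvement to a diagnostic and does not show that the primary analysis is invalid.

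**What to change.** - State that the GLMM assumes independence of weeks conditional on the drain.
- On the trial data, compare the Negative Binomial GLMM with and without a within-drain serial term (AR(1) over weeks, or a drain-by-month random effect) by likelihood ratio or AIC. Alternatively, test lagged autocorrelation of the GLMM's simulated residuals. As a guide, a lag-1 test on residuals adjusted for drain and week flagged about 3% of correct models and 59 to 87% of serial ones at mean 3 (37 to 69% at mean 1).
- Define a deviation from independence as support for that serial term. If it is supported, report the September and monthly estimates from the model that includes it.
- Keep the GEE, with robust standard errors, as a marginal sensitivity estimate and as the check of the independence assumed in the power calculation.

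The cost is a few lines of text and one extra model fit. No new data are needed.
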